## Aims and hypothesises

The **aim of the HopSCOTCH trial** is to develop, implement and trial an innovative shared-care approach to manage childhood obesity. We will compare outcomes for 3–10 year old obese children randomised to a shared-care model (general practitioners working with paediatric obesity specialist, consisting of a paediatrician and dietician - ‘intervention’ group) with outcomes for those receiving usual patient-driven primary care (‘control’ group).

We **hypothesise** that:

1. Compared to the control group, the intervention children will demonstrate better outcomes at 15 months in terms of lower:

i) Relative BMI, measured as a z-score (primary outcome)

ii) Percentage body fat

iii) Waist circumference

2. Compared to the control group, the intervention children will not show evidence of harm (ie poorer health status, body satisfaction, or global self-worth) at 15 months.

3. The intervention will be acceptable and feasible to (i) parents, (ii) general practitioners, (iii) general practice staff, and (iv) the obesity specialists.

## Methods and Design

### Approval and registration

The project is funded by the National Health and Medical Research Council of Australia (Project Grant 491212). It has been approved by the Royal Children’s Hospital Melbourne Human Ethics Committee (28017) and The University of Melbourne Human Research Ethics Committee (0827435).

### Design

HopSCOTCH is a randomised controlled trial of a shared-care intervention versus usual care in obese children (see Figure 1). The trial commenced in April 2008 and will run until December 2011. This period encompasses participant recruitment, baseline data collection, intervention delivery, follow up data collection (15 months post-recruitment, equating to approximately 12 months post-intervention) and data analysis.

**Figure 1 F1:**
[figure not shown]
Graphical depiction of components of the HopSCOTCH trial.

### Participants

Participants are (1) 120 children aged 3–10 years, identified as obese according to the United States Centres for Disease Control (CDC) charts (≥95^th^ age- and sex-specific percentile) [28]; and (2) their parents. Children were identified through participating general practitioners (GPs).

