#### *Randomisation and blinding*

Randomisation occurred via a concealed, computerised random number sequence stratified by general practitioner and pre-generated by the Clinical Epidemiology and Biostatistics Unit at the Royal Children’s Hospital. Once enrolled (i.e. on receipt of written informed consent and baseline questionnaire) a research assistant, who was not otherwise involved with the trial, randomised children to either the shared-care or usual-care arm. All families were advised of their child’s allocation by a mailed letter. All outcome measures were collected by researchers blinded to the child’s allocation status.

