### Sample size

The target sample size was calculated to detect a mean difference of 0.3 BMI z-score units at 15 months (comparable to published mean changes seen from specialist obesity clinics[4]) between arms with 80% power at 5% (2 sided) level of significance. Allowing for 10% loss to follow-up, we aimed to recruit 172 children.

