### Data Analysis

Analyses will be by ‘intention to treat’ at the level of the individual child. Linear regression will be used to compare quantitative outcomes between the trial groups adjusting for confounders and baseline measures of the outcomes where these are available, using an analysis of covariance approach. Logistic regression will be used to compare dichotomous outcomes.

Confounders selected *a priori* for multivariable models will include child sex, age at randomisation, and family socioeconomic status, which will be assigned according to postal code of residence using the Index of Relative Socioeconomic Disadvantage (mean 1000, s.d. 100) from the Australian Bureau of Statistics census-based Socio-Economic Indexes for Areas (SEIFA) [36].

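### The protocol describes 120 participants but states power only for a target of 172; the two numbers are not reconciled, and on the same inputs 120 children give less than 80% power

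*Protocol article*

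**What the plan says.** The Participants section of the protocol article gives the study population as a fixed number: "Participants are (1) 120 children aged 3–10 years, identified as obese".

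The Sample size section gives a different one. "The target sample size was calculated to detect a mean difference of 0.3 BMI z-score units at 15 months", "between arms with 80% power at 5% (2 sided) level of significance", and then: "Allowing for 10% loss to follow-up, we aimed to recruit 172 children". It ties the 0.3 to mean changes reported from specialist obesity clinics.

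The Data Analysis section plans linear regression "adjusting for confounders and baseline measures of the outcomes where these are available, using an analysis of covariance approach". Table 1 shows BMI measured at both baseline and outcome, so baseline adjustment is available for the primary outcome.

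The article does not state the SD behind 172, the allocation ratio or a baseline-outcome correlation.

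**The concern.** A reader who wants to know how well powered the described trial is finds one power figure, and it is attached to a sample 52 children larger than the one described: 172 − 120 = 52, and 52/172 = 30%. The article does not say whether 120 is the number enrolled, a revised target or something else.

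What is at stake is how the primary result is read. The 0.3 is the benchmark taken from specialist clinics, and the Economic evaluation section makes the full economic analysis conditional on the intervention being effective. If a non-significant result is taken to come from a test with 80% power for 0.3, it will look like stronger evidence against shared care than 120 children may be able to supply.

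**Working it through.** **Inputs from the article.** Difference 0.3; power 80%; two-sided 5%; loss 10%; target 172; participants described 120; two arms.

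**Assumptions, because the article does not give them.** 1:1 allocation; the 172 calculated for an unadjusted two-sample comparison; SD back-solved.

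**Step 1: reproduce 172.** It cannot be reproduced from stated inputs alone, so solve for the SD.
- Completers: 172 × 0.9 = 154.8, or 77.4 per arm.
- Normal approximation: SD = 0.3 × √(77.4/2) / (1.960 + 0.842) = 0.666. With the t distribution it is 0.662.
- Check with SD 0.664: n per arm = 2 × (0.664 × 2.802/0.3)² = 76.9, rounded up to 77; total 154; 154/0.9 = 171.1, rounded up to 172.

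So 172 is internally coherent at an SD of about 0.66.

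**Step 2: the same inputs at 120** (SD 0.662, t distribution).

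| | Per arm analysed | Power for 0.3 | Difference detectable with 80% power | 95% CI half-width |
|---|---|---|---|---|
| 172, 10% loss | 77.4 | 80% | 0.30 | 0.21 |
| 120, 10% loss | 54 | 65% | 0.36 | 0.25 |
| 120, no loss | 60 | 69% | 0.34 | 0.24 |

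**Step 3: does the result hang on the back-solved SD?** Not if the same SD, allocation and loss apply to both sample sizes, because they cancel. The standardised effect falls from 2.802 to 2.802 × √(120/172) = 2.340, and power is Φ(2.340 − 1.960) = Φ(0.380) = 65%. The detectable difference is 0.3 × √(172/120) = 0.36. What does not cancel is a change of analysis between the sample-size calculation and the trial.

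**Step 4: allow for the planned ANCOVA.** If 0.66 is a raw SD, the residual SD is 0.662 × √(1 − r²), where r is the correlation between baseline and 15-month BMI z-score. At 54 per arm:

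| r | Residual SD | Power for 0.3 |
|---|---|---|
| 0 (or 0.66 is already residual) | 0.66 | 65% |
| 0.5 | 0.57 | 77% |
| 0.6 | 0.53 | 83% |
| 0.7 | 0.47 | 90% |

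Power of 80% at 54 per arm needs a residual SD of 0.55 or less, which corresponds to r = √(1 − (0.551/0.662)²) = 0.55 or more.

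**The case against.** The strongest reply is that these are two different quantities. The Sample size section speaks in the past tense of a target and an aim, and the recruitment and randomisation sections describe work already done. The likely reading is therefore that 172 was sought and 120 were enrolled. On that reading nothing is miscalculated, and the article does not claim 80% for 120. This stands, and it rules out two inferences that a reader might draw: that the 172 is an arithmetic error, and that the authors assert 80% power for 120 children. It does not remove the gap. The Participants section does not say that 120 is the enrolled number, and if it is, a 30% shortfall passes without comment beside a power figure that it has overtaken.

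A second reply is that the primary analysis adjusts for baseline, so 120 may be enough. This also stands as a possibility: Step 4 of the working shows power above 80% at correlations of 0.6 and 0.7. For that reason the documents do not support the stronger inference that the trial is definitely underpowered at 65%. Equally, the article gives no correlation, does not make this argument, and does not say whether the 172 already allowed for adjustment. If it did, the adjustment has been spent and power stays near 65%.

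A third reply is that an article may leave the SD to the full protocol. Agreed: its absence is not the point here. The point is two printed numbers that do not fit together.

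**Conclusion.** The concern holds as an unreconciled sample size. The direction is free of assumptions about the SD: if 172 children are needed for 80% power, 120 give less on the same inputs. The size depends on one matter that the article leaves open. On the original inputs, power for 0.3 is about 65–69%, depending on loss, so roughly one true effect of that size in three would be missed. If the SD behind 172 was raw, baseline adjustment lifts power with 10% loss to between 77% and 90% for correlations of 0.5 to 0.7. The 65% is thus one end of a range and should be quoted as such. The estimate, the type I error and the analysis model are unaffected; what needs correcting is the power claim and the reading of a null result that would rest on it.

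**What to change.** 1. In the Participants and Sample size sections, label 172 as the original target and 120 as the enrolled or revised number, whichever is true, and acknowledge the difference.
2. Replace the 80% statement, as it applies to this trial, with the power and detectable difference for 120 under the planned ANCOVA. State the SD used, whether it is raw or residual, and the baseline-outcome correlation. If no correlation can be supported, give the unadjusted figures (about 65% and 0.36 with 10% loss) and a range over plausible correlations.
3. State that a non-significant primary result will be interpreted from its 95% confidence interval against 0.3, and not from the original power figure.

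This takes a few sentences. It needs no further enrolment and no change to the design or analysis; the only cost is a stated power that may be less favourable.

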### GP recruitment and training

To recruit GPs, HopSCOTCH was widely advertised through the Royal Australian College of General Practitioners and the Victorian general practice research network ‘VicReN’ e-bulletins/newsletters. Personalised invitations were also sent to GPs who previously participated in the LEAP 1 and LEAP 2 trials [10,29]. Of the 70 GPs who initially expressed interest, 35 GPs across 22 practices decided to take part.

GPs attended a 2½ hour group training session for instruction in the “stages of change” model [30] and training in brief, solution-focused family therapy [31]. GPs were shown role model scenarios of GPs using solution-focused therapy in consultations for healthy family lifestyle and given the opportunity to mimic these skills themselves with colleagues in role play scenarios designed by the research team. GPs also completed readings on current obesity management, followed by a brief online quiz to test their knowledge and training in measuring protocols. Those delivering the intervention received one-on-one training in how to use the specially designed shared-care software. GPs were provided with the following remuneration for their time and for bulk-billing all shared-care patients: $220 for attending the training sessions; $25 per child recruited from their practice; and $75 for GPs that saw shared-care patients five times and an additional $75 if they saw them eight or more times.

### Recruitment of children

To recruit children, HopSCOTCH was publicised in participating practices through posters, brochures and practice staff. Trained general practice staff opportunistically offered to weigh and measure children using calibrated digital scales and rigid stadiometers supplied by the research team. Eleven practices also sent letters to all of their in-age children inviting them to attend a dedicated weigh and measure session run by the research team or practice staff at the practice. With parent assent, their contact details and child anthropometry data were then mailed or faxed to the research team. Upon receipt, the research team calculated each child’s BMI and BMI percentile. Provided parents had left contact details, ineligible children’s families were sent a letter informing them of their ineligibility, while eligible families were telephoned to propose participation in the trial. Interested eligible families were mailed a parent information sheet, consent form and parent baseline questionnaire. Upon receipt of the written informed consent and the parent baseline questionnaire, families were enrolled in the trial.

### Inclusion and exclusion criteria

#### *Inclusion criteria*

Eligible families included children who met both the following requirements:

1) BMI ≥95^th^ for age- and sex-specific percentile according to the CDC charts, placing them in the obese range; and

2) aged between 3 and 10 years (i.e. up to but not including their 11^th^ birthday).

#### *Exclusion criteria*

Children were excluded if they met any of the following criteria:

1) receiving ongoing weight management in a secondary or tertiary care program;

2) a known endocrine or genetic cause for their obesity;

3) a major disability or health condition judged by parents and/or researchers to preclude meaningful participation;

4) their family did not speak sufficient English to complete questionnaires and participate in the trial.

#### *Randomisation and blinding*

Randomisation occurred via a concealed, computerised random number sequence stratified by general practitioner and pre-generated by the Clinical Epidemiology and Biostatistics Unit at the Royal Children’s Hospital. Once enrolled (i.e. on receipt of written informed consent and baseline questionnaire) a research assistant, who was not otherwise involved with the trial, randomised children to either the shared-care or usual-care arm. All families were advised of their child’s allocation by a mailed letter. All outcome measures were collected by researchers blinded to the child’s allocation status.

### Intervention arm

#### *Shared-care software*

A web-based shared-care software was designed with the goals of 1) allowing the obesity specialists and GPs to collaborate and communicate closely in the care of their patients, 2) providing a structured yet efficient approach to weight management care, and 3) providing a mechanism that allows both GPs and specialists to record and track patient progress simultaneously. The software’s weight management care plan consists of five steps: 1) recording anthropometry, 2) reviewing BMI change using an online chart to plot and track BMI visually over time against percentile charts, 3) assessing and tracking progress and motivation, 4) reviewing care plan (i.e. issues and goals), and 5) providing educational resources.

The HopSCOTCH software, developed in collaboration with Pen Computer Systems Pty Ltd (PCS), was designed to support specialist and GP management of children with obesity and to facilitate communication of information between the health care providers involved. Specifically, the HopSCOTCH system provides notification and communication between providers of care, access to patient information for care team members via the shared web-based HopSCOTCH record, obesity assessment and management tools, and help in developing a detailed management plan and history. Printouts of plans, educational resources and patient summaries can also be obtained. HopSCOTCH is launched from a desktop application, the PrimaryCare Sidebar®, a proprietary product of PCS. The PrimaryCare Sidebar® sits on the right of the screen (by default) and contains a series of panels, each with links to a range of primary care software tools. The panels allow the tools to be grouped into logical areas of health care. The HopSCOTCH system is accessed via the PCS Linked Care^TM^ panel.

### Obesity specialist consultation

The shared-care intervention involved each family (at a minimum the index child and one parent/guardian) attending a single one-hour session at Melbourne’s Royal Children’s Hospital, where they saw the obesity specialist team comprising a paediatrician and a paediatric dietician who specialise in childhood obesity and weight management. Prior to the appointment, researchers extracted clinically-relevant information about the child and family from the baseline questionnaire, including family history, medical history, daily diet, physical activity and sedentary activities, and scored multi-item scales (see Additional file 1). These data were entered into a summary, with abnormal values flagged, in order to both save time on history-taking and to provide additional information that would not normally be available during a single first clinical consultation (see completed example Additional file 1). This allowed the team to devote more consultation time exploring lifestyle modification, rather than primarily information gathering.

At the appointment, a researcher first measured the child’s height, weight and percentage of truncal fat. The paediatrician then interviewed the child and family, taking a clinical history and examining the child using a standard protocol to identify possible causes and co-morbidities of obesity. The dietician then undertook a detailed dietary history and outlined general principles of healthy eating, offering targeted advice based on the child and family’s eating patterns. Physical and sedentary activities were assessed and, together, the paediatrician and dietician then discussed the lifestyle changes required that would most likely assist in successful weight management for the child. This advice focussed on family change and support, in accordance with research showing beneficial results to the child when the parents are involved [32], and is consistent with current recommendations that, for most obese children, BMI reduction is best achieved by maintaining, rather than losing, weight as the child grows [33]. Details of the specialist consultation, including the clinical summary and pathology results (if applicable) and an initial care plan, were then entered into the shared-care software.

If clinically indicated, parents/guardians were asked to bring their child to the Pathology Department at the Royal Children’s Hospital within the next 2–3 weeks for standard metabolic tests such as a check of thyroid function. These results were also entered into the shared-care software so the GP could access them.

### GP consultations

After the specialist appointment, a follow-up appointment with the child’s GP was scheduled by the research team. Both the specialist and research team encouraged families to see their GP for regular (i.e. every 4–8 weeks) weight management consultations for a year following the specialist consultation. Information from the obesity specialists was available to all GPs via the shared-care software, including the family’s customised care plan.

The weight management GP consultations were designed to: 1) review lifestyle and BMI progress; 2) identify and solve problems where possible; and 3) set new goals using brief solution-focused techniques. The obesity specialists were available to the GP on an ‘as-needed’ basis throughout the trial. At the 6-month point, the obesity specialists formally reviewed each family’s progress using the synchronised software, with a focus on solutions and guidance for GPs. Each family’s review generated a one-page letter that was sent to the treating GP.

### Control arm

Participants in the usual-care (control) arm were not offered an obesity clinic appointment or identified as being in the trial to their GP. Parents were informed that they were free to seek assistance with their GP or with any other service. Should they present to their GP, the GP would be able to implement their usual clinical care and utilise skills gained in the training process, but they were not able to access the shared-care software to track progress, educational resources or access support from the obesity specialists regarding these patients.

### Measures and training

Table 1 summarises all outcome measures for the trial, with the primary outcome being BMI expressed as kg/m^2^[33]. All outcomes will be measured at 15 months post-randomisation, equating to approximately 12 months after the clinical consultation for the intervention children.

**Table 1 T1:** Primary and secondary outcome measures for the HopSCOTCH trial

Construct	**Time Point**		**Measure**	**Additional information**
	**Baseline**	**Outcome**		
**Primary Outcome**				
Body Mass Index (kg/m^2^)	**•**	**•**	Portable rigid stadiometer (model IP0955, Invicta, Leicester, UK); measured Calibrated digital scale (model TITHD646, Tanita, Toyko, Japan); measured	Height is measured twice and the average used; if the values differ by >0.5 cm a third measurement is taken and the average of the two closest values used. Weight, while wearing light clothing, is measured once at baseline, and measured twice at outcome. Average weight used at outcome; if the values differ by ≥0.2 kg a third measure was taken and average of the two closest values used. BMI is calculated as weight (kg)/(height (m)2). BMI z-score is calculated according to the US Centers for Disease Control (CDC) reference values [28], using the Stata ‘zanthro’ function.
**Secondary Outcomes**				
Waist circumference		**•**	Lufkin Executive Steel Tape (W606PM); measured	Average of two waist measurements; if they differ by ≥1 cm, a third measurement is taken and the mean of the two closest used.
Body fat (%)		**•**	Tanita Digital Body Composition Monitor (BC-351)[37]; measured	Average of two body percentage fat measurements.
Blood pressure/ heart rate		**•**	Welch Allyn ProBP3400; measured	Three blood pressure/heart rate readings are taken at least two minutes apart on the right arm with the child sitting; the average of the two closest readings is used.
Nutrition		**•**	4 day food diary; parent report	Parents report child’s consumption of each of 17 food and drink items (0, 1, 2, >2 times) for two weekdays and two weekend days. Dichotomous (“yes” v “no”) variables are derived for five “healthy behaviours” (high fruit, vegetables, and water; low fatty/sugary foods and non-diet sweet drinks) for each day. The number of healthy behaviours per day are summed to give a score between 0 and 5 (higher score indicating more healthy behaviour).
Physical activity		**•**	Actical Accelerometer (Mini Mitter); measured	Worn for 7 full days; ≥5 valid days required. Valid days have ≥10 hours of non-missing data between 6 am-11 pm. Missing data are segments with ≥20 minutes of consecutive “0” counts, or counts >0 that are constant for ≥10 minutes. Outcomes across all valid days: mean activity counts/min, and % time spent in moderate to vigorous physical activity.
Health status	**•**	**•**	Paediatric quality of life inventory (PedsQL 4.0); self report and parent-proxy versions [38]	Parent-completed 23-item scale that yields total, physical summary, and psychosocial summary scores, each with a possible range of 0–100 (100 = best possible health); quantitative variable.
Body dissatisfaction		**•**	Body figure perception questionnaire; self report [39]	Child picture scale of 1–7 (1 = underweight, 7 = obese) from which child picks perceived and ideal selves. “Perceived” minus “Ideal” self yields a discrepancy index, with positive and negatives scores representing desires to be thinner and fatter, respectively.
Physical appearance and self worth		**•**	Modified from Harter’s perceived competence scale; self report	Six pairs of statements with binary response format; children choose the statement from each pair that is closest to their competence. Each of the 6 responses is then coded as being either “positive/better perception” or “negative/worse perception”. The 6 responses are analysed as a single outcome.
Behaviour		**•**	Strengths and difficulties questionnaire [40]; self report	Parent-completed 25-item scale that yields scores for conduct problems, emotional symptoms, hyperactivity, peer relationships and pro-social behaviour.
Parent Readiness to change	**•**	**•**	Parent’s readiness to change child’s weight[41]; self report	3 items, each with a possible 5 responses (strongly agree – strongly disagree).
Parent BMI		**•**	Weight (kg)/(height (m)2); measured and self report	Baseline values reported for self and partner by responding parent. Values at 12 months measured for the parent(s) present with the child and reported; measured data used preferentially.

All researchers involved in baseline and outcome measurements were trained by researchers experienced in conducting similar measurements in the community from other research trials and longitudinal studies in childhood obesity. Researchers were trained at a single one-hour session where each measurement was demonstrated and repeatedly practised to ensure accuracy, competency, and reliability.

